**Metformin Group**

In the Metformin group, starting dose of Metformin will be 500mg once a day and increased gradually over two (2) weeks, to meet glycaemic targets of FBS < 5.1 mmol/L, 1HPG < 10.0mmol/L and 2HPG < 8.5 mmol/L.

The maximum dose will be 2500mg per day. Insulin will be added if targets cannot be reached on metformin alone at maximum doses. Subjects that receive supplemental insulin will be excluded from the metformin group and analyzed for the purpose of this study as treatment failures. The quantity of supplemental insulin will be documented for analysis.

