**SPECIFIC OBJECTIVES**

- To determine and compare blood glucose profile in pregnant women treated with metformin versus insulin.
- To determine the additional insulin requirements and the blood glucose profile in subjects who may require supplemental insulin in the metformin group.
- To measure and compare maternal weight gain in the index pregnancy between mothers treated with metformin versus insulin.
- To measure and compare birth weight between babies in the metformin and insulin groups.

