**JUSTIFICATION**

Studies in countries like United States of America (USA), Australia, Canada and India have found metformin an effective and cheaper alternative to insulin. Genetic variations exist in the pathogenesis of diabetes mellitus as well as in the metabolism of metformin. Consequently results from one area may not be applicable in another. It is therefore important to do a Ghanaian study. There is no published data on the use of Metformin in pregnancy for glycaemic control in Ghanaians. The role of an effective but cheaper and more convenient to use medication in the control of any medical condition in a low – middle income country like Ghana cannot be overemphasized. Poor patient follow-up and monitoring in Ghana makes the use of drugs that do not require frequent monitoring, a preferred option at all times to those requiring frequent monitoring.

Insulin is less affordable and not readily available at all times. The need for refrigeration for effective insulin storage and use in developing countries is associated with difficulties. Unlike insulin, metformin does not require refrigeration for effective storage. Metformin is readily available and its oral administration is tolerable to many patients.

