**Treatment failures**

Supplemental insulin for treatment failures in the Metformin group will be prescribed according to the same protocols in the insulin group.

DATA COLLECTION

Basic demographic data will be recorded. They will be followed through their index pregnancy, with 2-weekly blood glucose checks in hospital. All laboratory samples will be collected and analyzed at the diabetes research laboratory by staff of the same laboratory. Venous blood will be used for blood glucose profile analysis. Analysis of Fasting Blood Glucose (FBG), one- hour post-prandial glucose (1HPG), two- hour post-prandial glucose (2HPG) will be done using the Mindray BS-400^®^ (Mindray Medical Int. Ltd, China) chemistry analyzer. The method for glucose determination will be enzymatic photometric testing. Urinalysis, weight records (using Seca^®^(gmbh&Co. Kg Germany)) and cost of treatment will also be documented. The optimal dose of metformin required for optimal glycaemic control will be recorded for each patient. Peri-partum events like gestational age at delivery, type of delivery, fetal birth weight, and NICU admissions will be retrieved from patient notes.

STATISTICAL ANALYSIS

In analyzing the data, summary statistics will include appropriate tables and charts. Categorical data will be represented by pie and bar graphs and continuous data with histograms.

For inferential statistics, significant difference of mean observations using one-tail student’s t-test and z-score for differences in proportions where applicable. The differences in trends of glycaemic profile over time between the study groups will be assessed by two-way repeated measures analysis of variance (ANOVA).

Significance level (p-value) will be set at α = 0.05. Data analysis will be done using statistical package for social science **(SPSS** version 20).

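### Insulin in the metformin group is tied to failure at the fixed 2500 mg maximum, with no written rule for a woman who cannot tolerate that dose and no recording of adverse drug effects, hypoglycaemia or reasons for dose change

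*Protocol*

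**What the plan says.** In the Metformin Group section the "starting dose of Metformin will be 500mg once a day and increased gradually over two (2) weeks", the aim being to reach fasting, one-hour and two-hour glucose targets. The ceiling is a number: "The maximum dose will be 2500mg per day". The rule for adding insulin follows directly: "Insulin will be added if targets cannot be reached on metformin alone at maximum doses". A woman who receives supplemental insulin leaves the metformin group and is analysed as a treatment failure. For her, "The quantity of supplemental insulin will be documented for analysis".

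One of the Specific Objectives depends on these women: "To determine the additional insulin requirements and the blood glucose profile in subjects who may require supplemental insulin in the metformin group".

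On follow-up, Data Collection says: "They will be followed through their index pregnancy, with 2-weekly blood glucose checks in hospital". On metformin dosing it adds: "The optimal dose of metformin required for optimal glycaemic control will be recorded for each patient". The other items there are demographics, the glucose profile, urinalysis, weight, cost of treatment and peri-partum events. Expected Outcome lists glycaemic measures, birth weight, maternal weight gain, caesarean rate and neonatal intensive care admission. The Abstract adds birth trauma.

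**The concern.** Because the ceiling is fixed, the insulin rule covers a woman who reaches 2500 mg and still misses her targets. It does not cover a woman who misses them at a lower dose that she cannot exceed, or one who has to stop metformin. Two things are at stake.

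- **Care.** Under Eligibility criteria, every participant has already met the hospital's threshold for starting insulin. The uncovered woman is one whom the hospital would otherwise be treating with insulin.
- **Interpretation.** In this trial, receiving insulin moves a woman out of the metformin group. An unwritten, clinician-by-clinician decision about intolerance therefore helps to decide who is in the two-hour glucose comparison, which is the primary outcome, and in the weight and delivery comparisons. It also mixes two kinds of women in the supplemental-insulin objective.

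Separately, the protocol would have no systematic description of how either treatment was tolerated. Yet Background names hypoglycaemia among the disadvantages of insulin, and the Problem Statement names possible metformin toxicity.

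**Working it through.** The protocol gives no figure to reproduce here, so the check is mainly a comparison of its sections.

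**1. Is there any other route to insulin?**

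- Metformin Group: one trigger, at a maximum defined in the same paragraph as 2500 mg a day. Reading it as the maximum tolerated dose would add a word that the text lacks.
- Exclusion criteria: contraindications to metformin, at entry only.
- Treatment failures: how supplemental insulin is prescribed, not when intolerance should lead to it.
- Insulin group: admission and re-titration for women who miss targets on insulin. No matching step exists for metformin intolerance.
- Study Design: routine antenatal visits, with glucose checked under existing protocols. This is usual care, not an intolerance rule.

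No section covers dose reduction, stopping metformin or switching.

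**2. What follows for a woman who misses targets below 2500 mg and cannot go higher?**

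| Action | Result |
|---|---|
| Rule followed to the letter | Stays on metformin, above target, in the metformin group |
| Insulin given under usual care | Leaves the metformin group and is counted as a treatment failure |

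Her place in the comparison depends on a decision that the protocol does not describe.

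**3. Can the listed data separate her from a failure at full dose?** Partly. Metformin dose and insulin quantity are both recorded, so insulin together with a dose below 2500 mg would stand out. But the item is the optimal dose for control, which is unclear for a woman who never reached control, and no reason is recorded.

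**4. Are drug effects listed anywhere?** No maternal adverse drug effect, hypoglycaemic episode or reason for a reduction or stop appears in Specific Objectives, Data Collection or Expected Outcome. Two-weekly venous glucose can show a low value at a visit but not an episode between visits. Birth trauma, neonatal admission and caesarean rate are neonatal or obstetric outcomes.

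**5. Arithmetic for scale.** Inputs: 47 per group required and 52 recruited (Sample Size Determination); entry at 20 to 30 weeks (Eligibility criteria); two-weekly checks (Data Collection); powered comparison at 34 weeks.

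- Weight of one woman: 1/52 = 1.9%; 1/47 = 2.1%.
- Women affected, under *assumed* rates of intolerance leading to insulin: 2% × 52 = 1.04; 5% × 52 = 2.6; 10% × 52 = 5.2, so about 1, 3 and 5 women. The allowance for non-response is 52 − 47 = 5.
- Contacts by 34 weeks: (34 − 30)/2 = 2 to (34 − 20)/2 = 7, with more before delivery.
- What a descriptive table could show: with zero events, the exact two-sided 95% upper limit is 1 − 0.025^(1/n), which is 7.5% for n = 47 and 6.8% for n = 52. Only common effects can be described.

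**The case against.** The strongest reply is that the protocol states one trigger without forbidding others. Participants already qualify for insulin, routine antenatal care continues, and Ethical Considerations commits to standard protocols for research in human subjects. A reader might infer from the insulin rule that intolerant women would be left untreated. The documents do not support that: insulin is these women's default care, and its use is the likelier course. What stands is that no section writes the rule down, and that giving insulin has a consequence in the analysis.

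A reader might also infer that failures from intolerance and failures at full dose would be wholly indistinguishable. That goes too far, because metformin dose is recorded for each patient.

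Third, the recording gap is an omission that contradicts no stated objective. Hypotheses, Aim and Specific Objectives contain no safety claim, and the rationale says that metformin's safety has been shown elsewhere. It would therefore be wrong to call this a safety claim left untested. The questionnaire mentioned under Ethical Considerations is not shown and may hold some of the items, and patient notes may recover others, though not in a standard way.

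Finally, the protocol gives no evidence on how often intolerance occurs. The remark in Justification that metformin's "its oral administration is tolerable to many patients" is about the convenience of the oral route and cannot serve as a rate. This limits the priority of the point. It does not supply the missing rule, and an unseen analysis plan could neither authorise insulin nor analyse reasons that were never collected.

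**Conclusion.** The point holds as a gap in a treatment rule and in data recording. The insulin trigger omits intolerance below 2500 mg a day. Because insulin use removes a woman from the metformin group, that omission affects the primary and secondary between-group comparisons as well as the supplemental-insulin objective. Maternal drug effects and reasons for dose change are not listed for either arm.

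No size of effect is claimed. The 2% to 10% range in the working is an assumption, used only to show that the number of women could be anywhere from one to about the whole non-response allowance. The conclusion rests on reading the maximum as the stated 2500 mg, and on the unseen questionnaire not already covering these items. It is a cheap improvement of low priority.

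**What to change.** **Metformin Group.** Add insulin if targets are not met at 2500 mg a day or at the highest tolerated dose, or if metformin has to be stopped. Record the reason as intolerance or missed targets. Keep women given insulin for either reason in the metformin arm, as randomised, for the between-group comparisons, and report the two reasons separately. Without this last step, the wider trigger would send more randomised women out of the primary comparison. It also fits the Aim, which already covers metformin combined with insulin.

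**Data Collection.** At the existing two-weekly contacts, ask the same questions in both arms: adverse drug effects, hypoglycaemia since the last visit, current dose, and the reason for any reduction or stop.

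**Expected Outcome.** Report these items descriptively by randomised arm with 95% confidence intervals and no hypothesis test.

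**Cost.** A few sentences, a few extra fields and one descriptive table, with no new visit or laboratory test. Self-reported effects may differ between arms because no blinding is described; identical questions reduce this but do not remove it.

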**AIM**

The aim of this study is to determine if metformin monotherapy or metformin in combination with insulin is more effective at attaining and maintaining glycaemic targets compared to insulin monotherapy in the management of gestational diabetes mellitus and type 2 pre-gestational diabetes mellitus in Ghanaians.

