**Exclusion criteria**

Exclusion criteria will include patients with insulin dependent Diabetes Mellitus and patients with contraindications to metformin therapy.

SAMPLE SIZE DETERMINATION

Power calculation: The power calculation is based on the difference in 2HPG expected between the metformin and insulin groups at 34 weeks gestation. Using the two sampled mean formula^34^, the estimated sample size was 47 per group. From pre-trial estimates the minimum difference in mean 2HPG levels between the two groups of 4mg/dl (0. 22 mmol/l) is required to give a power of 80% to the study at a significance level of α = 0.05.We recruited 52 in each group to allow for a 10% non-respondent rate

TREATMENT PROTOCOL

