**Insulin group**

In the Insulin group both soluble insulin and premixed insulin will be prescribed. There will be no brand restriction. Both premixed insulin and soluble insulin will be administered subcutaneously in the deltoid region. Total daily dose of premixed insulin at initiation will be calculated for most patients as 0.3 IU/kg body weight. However for patients admitted with high blood glucose levels they will be managed on sliding scale with soluble insulin their starting dose will be based on total daily requirement. The total daily dose will then be divided into two: two-thirds of the dose will be administered in the morning 30 minutes before breakfast and one-third of the daily dose will be administered in the evening 30 minutes before supper. The total dose of insulin will be titrated for each patient to achieve the above glycemic targets. Patients who may not achieve glycemic targets on their out-patient doses after attempts at titrations will be admitted to the ward and treated with soluble insulin to determine their new optimum insulin requirements. All patients will be educated by both nurses and doctors while on admission on the disease and self-administration of the correct doses of insulin before discharge.

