**EXPECTED OUTCOME**

It is expected that pregnant diabetics treated with metformin will have a lower 2HPG levels at the end of the study than those treated with insulin. The primary outcome is the difference in the 2HPG level between the metformin and insulin group. The rationale for selecting 2HPG is that by its mechanism of action, metformin is expected to have a more significant blood glucose lowering effect in the postprandial period than the fasting period. Hyperglycaemia in the prandial period is related to insufficient suppression of hepatic glucose output, poor insulin release and ineffective glucose disposal in target tissues (especially muscles) by insulin (insulin resistance) and metformin affect all these Biophases.^30-32^

Secondary outcomes to be measured include glycaemic profile (measured by FBG, 1HPG, and HB1AC), fetal birth weight, maternal weight gain and caesarean section rate which are expected to be lower in the metformin group, number of NICU admission which is expected to be higher in the insulin group. If found to be effective it may form the basis for developing a policy for Diabetes Mellitus care in pregnancy at primary and secondary level of healthcare instead of the current tertiary level of care.

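### Women randomised to metformin who receive supplemental insulin are taken out of the metformin group, so the primary 2HPG comparison is no longer randomised and can be biased, most likely towards metformin

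*Protocol*

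**What the plan says.** **Exclusion.** Protocol, Metformin Group: "Subjects that receive supplemental insulin will be excluded from the metformin group and analyzed for the purpose of this study as treatment failures". The trigger stands just before it: "Insulin will be added if targets cannot be reached on metformin alone at maximum doses". The targets listed there are for fasting glucose, 1HPG and 2HPG.

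**Insulin arm.** Protocol, Insulin group: "Patients who may not achieve glycemic targets on their out-patient doses after attempts at titrations will be admitted to the ward" for re-titration. Nothing there, or elsewhere, removes these women from the insulin group.

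**Primary outcome.** Protocol, Expected Outcome: "The primary outcome is the difference in the 2HPG level between the metformin and insulin group". The same section expects lower 2HPG on metformin. The sample size section adds the time point: "The power calculation is based on the difference in 2HPG expected between the metformin and insulin groups at 34 weeks gestation".

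**Aim.** Protocol, Aim, puts the question as follows: "determine if metformin monotherapy or metformin in combination with insulin is more effective at attaining and maintaining glycaemic targets compared to insulin monotherapy". The Abstract's statement of the aim also names the combination.

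**Analysis.** Statistical Analysis gives a one-tailed t-test for means and a repeated-measures ANOVA for trends between groups. The protocol nowhere says that women are analysed as randomised. The second specific objective describes insulin need and glucose profile in the women who need supplemental insulin.

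**The concern.** The exclusion happens after randomisation, depends on on-treatment glucose, and applies to one arm only. A metformin woman leaves her group because an earlier value of the outcome variable, or a close relative of it, was too high. An insulin woman with the same value is re-titrated, and no rule takes her out. What remains is a selected part of one arm against all of the other.

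This affects the primary 2HPG difference. It also affects any secondary outcome compared on the same groups: the other glucose measures, maternal weight gain, birth weight, caesarean section and NICU admission. The test is one-tailed and the protocol expects metformin to be lower, so a selection effect in the likely direction turns directly into false-positive results. The rule also conflicts with the aim: women on metformin plus insulin are part of the question but not of the metformin group that is compared.

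**Working it through.** **1. The plan's own figures.** The sample size section gives 47 per group for a 0.22 mmol/L difference, 80% power and α = 0.05, but no SD, so the 47 cannot be checked directly. Solving n = 2·SD²·(z_α + z_β)²/δ² for the SD:

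- One-sided: SD = 0.22 × √(47/2) / (1.645 + 0.842) = 0.43 mmol/L.
- Two-sided: SD = 0.22 × √(47/2) / (1.960 + 0.842) = 0.38 mmol/L.

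The 52 recruited is 47 × 1.10 = 51.7, rounded up.

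**2. Assumptions.** The documents give neither the share of metformin women who will need insulin (f) nor the correlation (ρ) between the control that triggers insulin and 34-week 2HPG. Both are assumed over a range. Earlier control and 34-week 2HPG are taken as bivariate normal, with no true difference between arms.

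**3. Expected bias.** If the worst-controlled fraction f leaves the metformin arm, and later treatment changes nothing, the metformin mean shifts by −ρ·φ(c)/(1 − f) SD, where c is the normal cut-off with upper tail f. At ρ = 0.5:

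- f = 10%: −0.5 × 0.1755/0.90 = −0.10 SD
- f = 20%: −0.5 × 0.2800/0.80 = −0.17 SD
- f = 30%: −0.5 × 0.3477/0.70 = −0.25 SD
- f = 45%: −0.5 × 0.3958/0.55 = −0.36 SD (−0.35 in simulation, where whole women are removed)

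At the implied SD of 0.43 this runs from 0.10 × 0.43 = 0.04 to 0.35 × 0.43 = 0.15 mmol/L, against the design difference of 0.22.

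**4. False-positive rate.** Simulation with 20,000 trials per cell, 47 randomised per arm, removal from the metformin arm only, then a one-tailed t-test at 5% for lower 2HPG on metformin. Repeat runs differ by about one percentage point.

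| Scenario | f = 10% | 20% | 30% | 45% |
| --- | --- | --- | --- | --- |
| ρ = 0.5, no effect of re-titration | 13% | 19% | 29% | 43% |
| ρ = 0.5, re-titration in the insulin arm closes half the gap | 9% | 12% | 15% | 20% |
| ρ = 0.5, gap closes fully | about 5% | about 5% | about 5% | about 5% |
| ρ = 0.3, no effect of re-titration | 9% | 12% | 16% | 22% |
| ρ = 0, no effect of re-titration | about 5% | about 5% | about 5% | about 5% |

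The gap is the difference in mean 34-week 2HPG between insulin women who missed targets earlier and those who did not. The rates do not depend on the SD, because the bias scales with it.

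**5. After the fix.** With every woman kept in her assigned arm, the same test gave 4.8% to 5.3% in every scenario checked (ρ from 0 to 0.7, f from 10% to 46%).

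**The case against.** **The women are not lost.** They are to be analysed as treatment failures, and the second objective reports their glucose profile and insulin need. The aim could also be read as two separate comparisons with insulin. A reader might infer that these women are deleted and the combination is never examined; the documents do not support that. What stands is narrower: both provisions describe the women separately, and no rule says how a failure enters a difference in mean 2HPG. Neither returns them to the randomised comparison.

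**Later treatment may undo the selection.** Insulin women who miss targets are re-titrated, and metformin failures receive insulin under the same protocol. This stands. The rates without a re-titration effect are upper scenarios for each correlation. If added insulin brought the removed women to the 2HPG of those who remain, or below it, the effect of removing them would vanish or reverse.

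**High correlations are doubtful.** The trigger includes fasting glucose, and the Pharmacodynamics section says that insulin is the more effective for fasting and metformin for postprandial hyperglycaemia. Some failures may therefore be fasting failures, less closely tied to 2HPG. This is a fair reason to give the ρ = 0.3 row weight and not to rely on correlations above 0.5.

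**The bias need not exceed the design difference.** A reader might infer that it does. That holds with an SD of 1.5 mmol/L, where 20% failures give 0.175 × 1.5 = 0.26 mmol/L. But with that SD the design would need about 575 women per group, one-sided. At the SD implied by 47 per group the bias at ρ = 0.5 stays below 0.22.

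**A statistical analysis plan may exist.** It is not at hand, and its absence is no fault. But the protocol sentence fixes the exclusion, and a plan that follows it takes over the problem.

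**Conclusion.** The exclusion is wrong as written and should be corrected before analysis. It depends on glucose, acts after randomisation, applies to the metformin arm only and conflicts with the aim. That conclusion rests on the text alone.

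The size rests on assumptions. At ρ = 0.5 the false-positive rate ranges from about 5%, if re-titration closes the gap fully, to between 13% and 43%, depending on the failure rate, if re-titration has no effect. The corresponding bias without a re-titration effect is about 0.10 to 0.35 SD. At that bias's upper end, the shift is roughly two-thirds of the design difference (0.15/0.22 = 0.68).

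It would go too far to say that the result will be biased towards metformin. That direction is the likely one, because the women removed had glucose above target, but it is not certain. Nor does the protocol state that insulin women who miss targets stay in their group for analysis; it simply gives no rule that takes them out.

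**What to change.** Replace the exclusion sentence in the Metformin Group section with: *All randomised women are analysed in the group to which they were assigned, whether or not supplemental insulin was given; this is the primary analysis.* Report the need for supplemental insulin separately, under the second objective. Label any metformin-monotherapy comparison supportive or exploratory; it remains relevant to the hypothesis of equal effectiveness.

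The cost is one sentence of protocol text plus that labelling. No extra data are needed: Data Collection follows participants through the pregnancy, and the second objective already requires these women's glucose profiles. No clinical rule changes.

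There is a downside to accept. The metformin estimate may look less favourable, and insulin rescue in the metformin arm may draw the two arms together, so the primary result speaks to starting on metformin with insulin added where needed, not to metformin alone.
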